### Criteria for discontinuing or modifying allocated interventions {11b}

*Medical safety concerns*: If a participant experiences any adverse events or medical complications that are directly related to the allocated exercise program, discontinuation or modification should be considered. This could include issues like musculoskeletal injuries, cardiovascular symptoms, or other medical conditions exacerbated by exercise.*Non-adherence*: If a participant consistently fails to adhere to the prescribed exercise regimen, it might be necessary to modify the program to better suit their schedule, preferences, or physical capabilities. Non-adherence can affect the efficacy of the intervention and overall study outcomes.*Technology issues*: Given the remote nature of the intervention, technical issues may arise that hinder the participant’s ability to engage effectively. In such cases, modifications to the technology setup or the exercise routine may be required.

### Strategies to improve adherence to interventions {11c}

*Personalized planning and goal setting*: Developing individualized rehabilitation plans based on participants’ unique characteristics and objectives enhances intervention adherence. Aligning rehabilitation goals with participants’ expectations and realistic capabilities fosters engagement and persistence. Tailored plans bolster participant motivation, increasing the likelihood of sustained intervention adherence.*Regular tracking and feedback*: Establishing systematic tracking mechanisms to monitor participants’ progress and achievements is imperative. Providing consistent feedback assists participants in recognizing their efforts and advancements. Positive reinforcement fosters affirmative behavior and aids participants in maintaining intervention adherence.*Mobile applications and reminder systems*: Leveraging mobile applications and reminder systems delivers timely prompts and guidance to participants. Mobile applications may encompass training regimens, video tutorials, and progress monitoring. Reminder systems, through short messaging service or emails, prompt participants to fulfill their intervention tasks. These technological tools heighten participant engagement with the intervention, mitigating forgetfulness and thus amplifying adherence.

### Relevant concomitant care permitted or prohibited during the trial {11d}

*Permitted concomitant care*: Participants are permitted to continue their routine medical care and consultations with their primary healthcare providers. Concomitant medications, advised exercises, and non-invasive interventions unrelated to the trial are allowed. These should be documented and reported to provide a holistic view of participants’ overall care.*Prohibited concomitant care*: During the trial period, participants are advised against engaging in any new therapeutic interventions, whether conventional or complementary, for chronic low back pain. This includes invasive procedures, surgical interventions, and experimental treatments targeting the same condition. Participants are encouraged to strictly adhere to the trial intervention and to refrain from initiating new concomitant care approaches without prior approval from the study investigators.

### Provisions for post-trial care {30}

If participants are injured as a result of this study, they may receive free treatment and/or compensation in accordance with Chinese law in case of injury in connection with this clinical study.

#### Outcomes {12}

### Primary outcome

The primary outcome is the mean pain intensity over the previous week assessed using an 11-point numeric rating scale (NRS;0 = no pain, 10 = unbearable pain) at 16 weeks after randomization. A higher score indicates higher pain intensity [25]. The between-group minimal clinically important difference (MCID) is 1.0 point on the NRS scale [26]. The within-group MCID is a 30% change from baseline [27].

#### Secondary outcomes

The disability and will be assessed using the Oswestry Disability Index (ODI). The ODI evaluated disability across 10 domains, encompassing pain intensity and functional abilities related to personal care, lifting, walking, sitting, standing, sleeping, sexual activities, social life, and traveling. Each domain was rated on a 6-point scale ranging from 0 to 5. A score of 0 indicated the highest level of functioning, while a score of 50 indicated total disability [28].The 36-Item Short Form Health Survey (SF-36), a widely used tool, assesses health-related quality of life and overall well-being across diverse populations. Developed by Wareldman and Ware in the early 1980s, it evaluates an individual’s physical, mental, and social health experiences across eight domains, including physical functioning and mental health. With 36 questions, responses are scored from 0 to 100, reflecting higher scores for better health status. Its brevity, versatility, and comprehensive health dimension coverage are notable advantages. The SF-36 finds applications in clinical practice, epidemiology, and health outcome studies, aiding in diagnosis, treatment, and policy decisions. Its widespread use allows for inter-study comparisons and meta-analyses, underpinned by robust psychometric properties, making it an invaluable tool for assessing health-related quality of life across diverse contexts [29].We will measure the angles of forward flexion, extension, and lateral bending in patients with CLBP using measurement tools within the Yinshan system.

In the control group, participants will be required to sign in and record their attendance. The intervention group utilized a WeChat mini program system to document treatment frequency and quality for the participants. This study excludes the use of drugs or invasive procedures, thereby minimizing the potential for adverse reactions. However, it is important to acknowledge that inadequate warm-up, excessive exercise intensity, or improper technique during exercises may exacerbate pain or cause muscle strain and fatigue. To promptly address any potential adverse reactions, participants will receive instructions to immediately contact us in case of physical discomfort. Patient satisfaction will be assessed using the Patient Satisfaction Questionnaire [30], a straightforward survey that measures treatment satisfaction on a scale of 1 to 5, with the following criteria: 1 = satisfied, 2 = somewhat satisfied, 3 = neither satisfied nor dissatisfied, 4 = somewhat dissatisfied, and 5 = dissatisfied.

### Participant timeline {13}

The participant timeline is presented in Table 1.

**Table 1 Tab1:**
[figure not shown]
Content for the schedule of enrolment, interventions and assessments

^a^*t*_*1*_, week 1; *t*_*2*_, week 2; *t*_*3*_, week 3; *t*_*4*_, week 4; *T*_*5*_, week 16

### Sample size {14}

With a non-inferiority design, the intervention group and control group had a 1:1 ratio of participants. In March 2023, we conducted a pilot study in the outpatient department of the First Affiliated Hospital of Sun Yat-sen University and collected a total of 21 subjects, including 15 in the intervention group and 6 in the control group, for a 4-week intervention. They were followed up 3 months later. The result yielded mean decreases of − 1.6 (SD = 2.0) for the intervention group and − 1.9 (SD = 1.9) for the control group on the NRS. With a significance level (*α*) of 0.05 and a power (1-*β*) of 0.9, considering a non-inferiority margin of − 1 and a difference (*δ*) of 0.3 in NRS decrease between the intervention and control groups, the PASS software (version 21) estimated that each group required 41 participants. Assuming a dropout rate of 20%, a total of at least 102 participants were needed for both groups.

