**Methods:**

In this trial, we will randomly assign 104 adults with chronic low back pain (CLBP) to either an intervention or control group, with 52 participants in each group. Both interventions will consist of three weekly 0.5-h sessions of core stability exercise (CSE). The intervention group will engage in home rehabilitation training utilizing key identification technology for movement, while the control group will perform supervised exercises in a hospital setting. Outcome assessments will be conducted at 4 weeks and 16 weeks after randomization. The primary outcome measure will be the change in pain intensity based on numeric rating scale (NRS scores) from baseline to 4 weeks. Secondary outcomes will include changes in physical function (measured by the Oswestry Disability Index (ODI)) and lumbar spine mobility as well as activity participation and treatment satisfaction.

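### The 41 per group fits only a home-training arm assumed 0.3 NRS points better; the pilot showed it 0.3 worse, and at that difference power is about 49%, not 90%.

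*Protocol article*

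**What the plan says.** All the inputs stand in the protocol article, Sample size {14}. The pilot is summarised as "mean decreases of − 1.6 (SD = 2.0) for the intervention group" and, again with a minus sign, "1.9 (SD = 1.9) for the control group on the NRS"; it had 15 and 6 participants. The design values are α and power "of 0.05 and a power (1-*β*) of 0.9", with no statement of whether α is one- or two-sided. The calculation is described as "considering a non-inferiority margin of − 1 and a difference" "of 0.3 in NRS decrease between the intervention and control groups, the PASS software (version 21) estimated that each group required 41 participants". The section ends: "Assuming a dropout rate of 20%, a total of at least 102 participants were needed for both groups". The Abstract gives a slightly larger enrolment: "we will randomly assign 104 adults with chronic low back pain (CLBP) to either an intervention or control group", 52 in each. Outcomes {12} says that a higher NRS score means more pain, so a larger fall is the better result.

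**The concern.** Two sign conventions appear to have been mixed. As raw change scores, intervention minus control is −1.6 − (−1.9) = +0.3, and on that scale positive is unfavourable to the intervention. A margin of −1 belongs to the opposite scale, intervention minus control in the size of the fall, where negative is unfavourable and the pilot difference is −0.3. Pairing +0.3 with −1 puts the expected result 1.3 points from the margin instead of 0.7. The required sample size varies with the inverse square of that distance, so the slip changes it by a factor of (1.3/0.7)² = 3.4.

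Non-inferiority is the declared design (Trial design {8}), and this section is the only justification given for the trial's size. If the pilot is right, the trial is about as likely to miss non-inferiority as to show it. A confidence interval straddling the margin would then be a likely result, and it would be hard to separate true inferiority from lack of power.

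**Working it through.** **Inputs (Sample size {14}).** SDs 2.0 and 1.9; margin 1.0; difference 0.3; α 0.05; power 0.90; allocation 1:1; dropout 20%. The sum of the two variances is 4.00 + 3.61 = 7.61, equivalent to a common SD of 1.951. Weighting by the pilot group sizes gives a pooled SD of √((14 × 4.00 + 5 × 3.61)/19) = 1.974.

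**Formula.** n per group = (z₁₋α + z₁₋β)² × (SD₁² + SD₂²) / D², where D is the distance from the expected difference to the margin. At one-sided 0.05 and 90% power, (1.645 + 1.282)² = 8.567.

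**Reproducing 41 (D = 1.3).**
- SD 2.0 in both groups: 8.567 × 8 / 1.69 = 40.6, so 41 (42 by the t test).
- SDs 2.0 and 1.9: 8.567 × 7.61 / 1.69 = 38.6, so 39 (40 by t).
- Pooled SD 1.974: 40 (41 by t).

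The plan's figure is therefore reproduced, but only at D = 1.3 and one-sided 0.05. At one-sided 0.025 the same distance needs 45 to 51 per group over SD 1.9 to 2.0.

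**The pilot direction as stated (D = 0.7).** 8.567 × 7.61 / 0.49 = 133.1, so 134 per group; over SD 1.9 to 2.0 the range is 127 to 141. At one-sided 0.025 it is 164 by the normal formula and 165 by t. After dropout, 134/0.8 = 167.5, so 168 per group and 336 in total.

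**A true difference of zero (D = 1.0).** 8.567 × 7.61 / 1.00 = 65.2, so 66 per group. This does not explain 41 either.

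**Power with 41 evaluable per group.** The standard error is √(7.61/41) = 0.431. For D = 0.7 the normal approximation gives Φ(0.7/0.431 − 1.645) = Φ(−0.02) = 49.2%. Noncentral t results with SDs 2.0 and 1.9:

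| True difference (intervention minus control, in NRS decrease) | D | 41 per group, one-sided 0.05 | 41 per group, one-sided 0.025 | 52 per group, one-sided 0.05 | 52 per group, one-sided 0.025 |
|---|---|---|---|---|---|
| −0.3 (pilot as stated) | 0.7 | 48.7% | 36.1% | 56.9% | 44.1% |
| 0 | 1.0 | 74.4% | 63.1% | 82.9% | 73.5% |
| +0.3 | 1.3 | 91.1% | 84.6% | 95.8% | 92.0% |

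The columns for 52 assume that nobody drops out. Over SD 1.9 to 2.0, the 48.7% ranges from 47% to 50% by t.

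**Dropout step.** 41/0.8 = 51.25, so 52 per group and 104 in total. The stated minimum of 102 leaves 102 × 0.8 = 81.6 evaluable, just short of 82.

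**The case against.** The strongest reply is that the cause is inferred. The article does not give the sign or the SD entered in the software, or whether α is one-sided, and its description of decreases with a minus sign is a double negative. That is fair as to mechanism. It does not rescue the figure: over the SDs and both α levels tried, the pilot direction as stated needs 127 to 173 per group. Reading the double negative literally would mean that pain rose in both pilot groups, which conflicts with the same section calling the quantity a decrease.

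A second reply is that the pilot is weak. With 15 and 6 participants, the standard error of the difference is 1.974 × √(1/15 + 1/6) = 0.95. The 95% interval around 0.3 against the intervention then runs from about 1.7 in its favour to 2.3 against it. The true difference may well be zero or favourable, so 49% is conditional on the pilot. This stands, and it is why power at zero belongs beside it. But the section takes its 0.3 from this pilot and gives no other reason to expect the home arm to do better.

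Two smaller points also stand. The 102 against 104 discrepancy is trivial, because the Abstract already enrols 104. And low power does not make every failure uninterpretable: a confidence interval lying wholly beyond the margin would still be informative.

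**Conclusion.** The concern holds. The stated inputs do not give 41 per group at 90% power. With the pilot direction as reported, 41 evaluable per group give about 49% power at one-sided 0.05, the more lenient of the two levels and the one that reproduces 41; at one-sided 0.025 they give about 36%. Even if all 52 per group were evaluable, power would be 57% or 44%. Reaching 90% would take 134 evaluable per group, more than three times the stated number. These figures assume the pilot SDs, a margin of 1.0, a true difference equal to the pilot's, and an unadjusted two-group comparison of change. That the cause is a reversed sign is an inference, though a strong one. The mismatch between inputs and result does not depend on it. The dropout rounding is a minor correction.

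**What to change.** Rewrite Sample size {14} as follows.

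1. Use one convention throughout: difference = intervention minus control in NRS decrease, margin −1.0, pilot difference −0.3.
2. State that α is one-sided and give its value, and name the SD used.
3. Restate the power of the 104-participant trial. With 41 evaluable per group at one-sided 0.05 it is about 49% at −0.3, 74% at 0 and 91% at +0.3.
4. If the sponsor wishes to plan on 0 or +0.3, say so and justify it against the pilot. If 90% power at −0.3 is wanted, the trial must be enlarged to about 336.
5. Replace the minimum of 102 with 104.

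A prespecified baseline-adjusted analysis could recover some of the lost power without more participants. The article gives no baseline-to-follow-up correlation, so the gain cannot be quantified here.

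Items 1 to 3 and 5 cost a protocol amendment and a less favourable stated power, with no extra participants. They leave the trial underpowered at the pilot difference, so item 4 is a real decision for the sponsor. Trial status describes a preliminary phase with recruitment still to begin, so on the article's own account the decision could be taken at the design stage.

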### Recruitment {15}

Recruitment will be advertised in notices posted in the clinic and on a social network platform (WeChat). The main inclusion and exclusion criteria will be included in our registration questionnaire. Possible eligible participants will be invited to come to the hospital for a physical examination and baseline assessment. Eligible participants will be assigned a number according to the sequence of their arrival at the hospital and then to the research assistant for random grouping. Participants will be informed of the time of treatment after the baseline assessment, so that they can arrange their schedule. Treatment content will be announced 3 days before the start of the intervention.

#### Assignment of interventions: allocation

### Sequence generation {16a}

For the randomization, a simple block randomization process was conceived and will be implemented by a trial assistant. After eligibility is confirmed, every participant will be assigned a unique number as an identifier. Sequence generation will be achieved using the IBM Statistical Package for Social Sciences (SPSS) version 23 software and stratified with a 1:1 allocation. The randomization list reports a progressive randomization number for randomized participants (from 1 to 20), and the treatment (intervention or control) will be assigned to the subject in either group.

### Concealment mechanism {16b}

The randomization tables will be generated by a research assistant who will not participate in the entire participant recruitment and treatment process and will be kept by another researcher who will not participate in the participant recruitment. The randomization tables will be published within 1–2 days of the intervention. This ensures that the researchers, therapists, and subjects in charge of recruitment do not know about the grouping before the intervention begins.

### Implementation {16c}

The trial assistant, who will not be involved in the entire treatment procedure, will generate and maintain the allocation sequence. The principal investigator will enroll and assign the participants to the groups according to their unique numbers. Once allocated, the participant will not be allowed to change their group.

#### Assignment of interventions: blinding

### Who will be blinded {17a}

It is not possible to blind the participants and the researcher due to the nature of the experiment’s design.

### Procedure for unblinding if needed {17b}

Not applicable as no blinding was used in this trial.

#### Data collection and management

### Plans for assessment and collection of outcomes {18a}

Data collection will be facilitated through an electronic questionnaire, with automatic storage in a network disk database (https://www.wjx.cn/newwjx/manage/myquestionnaires.aspx). This database will be subject to collaborative management by the research team. Subsequent data analysis will be conducted by a statistical analyst, ensuring blinding to both group allocations and intervention protocols.

### Plans to promote participant retention and complete follow-up {18b}

*Clear communication and participant engagement*: Establish open and transparent communication channels with participants from the beginning of the study. Clearly explain the study’s importance, goals, and expected outcomes. Maintain regular contact through WeChat to keep participants engaged and informed about the study’s progress. Emphasize the significance of their contribution to foster a sense of ownership and commitment.*Incentives and acknowledgments*: Offer appropriate incentives as a token of appreciation for participants’ commitment to the study. We plan to give the subject a lumbar pad worth about 50 yuan after completing the 4-week treatment. Recognizing their dedication can enhance their motivation to stay involved.

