### Experiment duration

The intervention spanned a total of 4 weeks, with participants engaging in 30-min training sessions three times a week. Clinical follow-up assessments were scheduled at week 4 and week 16. The research project is scheduled to take place from January 2024 to December 2025. The experimental flowchart is shown in the figure (Fig. 1).

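### The only named retention gift is a lumbar pad handed over after the 4-week treatment, so it may touch the week-16 pain score and does not reward week-16 follow-up (minor, cheap to fix)

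*Protocol article*

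**What the plan says.** All references are to the protocol article.

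- **Gift.** The section on retention and complete follow-up {18b} opens its incentive paragraph in general terms, "Offer appropriate incentives as a token of appreciation for participants’ commitment to the study", and then gives a single specific item: "We plan to give the subject a lumbar pad worth about 50 yuan after completing the 4-week treatment". No other gift and no other time point is named. The same section also plans "Maintain regular contact through WeChat to keep participants engaged and informed about the study’s progress", with no end date.
- **Assessments.** Under Experiment duration: "Clinical follow-up assessments were scheduled at week 4 and week 16". The intervention itself lasts 4 weeks.
- **Primary time point.** The Primary outcome section places the pain score "at 16 weeks after randomization". The Abstract (Methods) instead gives the change on the "numeric rating scale (NRS scores) from baseline to 4 weeks".
- **Analysis.** Statistical methods {20a} states intention-to-treat and plans comparisons of baseline with week 4, baseline with week 16, and week 4 with week 16.
- **Concomitant care {11d}.** During the trial, "participants are advised against engaging in any new therapeutic interventions, whether conventional or complementary, for chronic low back pain".

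**The concern.** There are two separate issues.

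First, a lumbar pad is not neutral in a back-pain trial. The protocol's own rationale mentions prolonged sitting and poor posture, the disability index has a sitting item, and the outcomes are self-reported by participants who know their arm. If the pad has any effect on pain, the week-16 score reflects training plus pad. If the arms also differ in how many people receive and use it, part of the week-16 difference between arms is a pad effect.

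Second, the gift appears in a section whose purpose includes complete follow-up, yet it is handed over when 12 weeks of follow-up remain. The one named material reward is spent before the assessment that is hardest to keep. On the natural reading, it also misses those who stopped training, whose week-16 data an intention-to-treat analysis needs just as much.

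**Working it through.** The plan gives no figure for this point, so there is nothing of its own to reproduce. The check is mainly a matter of setting the timings and conditions side by side.

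**1. Timing.** Treatment ends at week 4 and the last assessment is at week 16, so the gap is 16 − 4 = 12 weeks. The pad arrives at the start of this gap. It follows the treatment period, so the week-4 score should not be affected. It precedes the week-16 score, so two of the three planned comparisons (baseline with week 16, week 4 with week 16) span the period after the pad is given.

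**2. Who receives it.** The sentence ties the gift to the subject and to completing treatment. The natural reading is that those who do not complete do not receive it. The text does not say so outright and sets no session threshold; it could simply mark the end of the treatment period.

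**3. Could receipt differ between arms?** Yes, and the protocol gives reasons in both directions.
- Home participants choose their time and place, while controls attend at a fixed hour on three weekdays. The comparator section concedes that face-to-face sessions may not suit people with busy schedules. This points to more completion at home.
- The Abstract and Background say that home exercise without a therapist suffers from poor compliance or weaker long-term results. The new technology is meant to cure this, but that is what is being tested. This points to less completion at home.

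**4. Form of any bias.** Let p_H and p_C be the proportions in the home and control arms who receive and use the pad, and e its mean effect on week-16 NRS, taken as equal in the two arms. Then:

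shift in the between-arm difference = (p_H − p_C) × e

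If p_H = p_C, the shift is 0 whatever e is. The documents give neither p_H − p_C nor e. Purely as an illustration on assumed values, in NRS points:

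| Difference in receipt | e = 0.25 | e = 0.5 | e = 1.0 |
|---|---|---|---|
| 5 points | 0.0125 | 0.025 | 0.05 |
| 10 points | 0.025 | 0.05 | 0.10 |
| 20 points | 0.05 | 0.10 | 0.20 |

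The non-inferiority margin is 1 NRS point. The largest cell, 0.20, is a fifth of it, but requires e = 1.0. That equals the whole between-group minimal important difference in the Primary outcome section, and it exceeds half of either pilot decrease (1.0/1.6 = 0.63; 1.0/1.9 = 0.53). An effect that large from an item worth about 50 yuan is hard to credit. The table shows how the bias would scale and is not an estimate.

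**5. What remains when the shift is zero.** With equal receipt and use, the between-arm comparison is not shifted. The within-arm change from week 4 to week 16 would still mix persistence of training with any pad effect.

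**The case against.** The case on the other side is substantial, and most of it stands as a limit on the point.

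- **A reader might infer that the pad goes only to completers.** That is the natural reading, but it is not stated. The argument about differential receipt depends on it, or on unequal use.
- **A reader might infer that the pad breaks the concomitant-care rule.** The text does not support that. The rule is addressed to participants, gives invasive, surgical and experimental treatments as its examples, and allows for investigator approval. A token handed out by the investigators is not a treatment that a participant started alone, and nowhere is it called therapeutic. What stands is that supplying a back-related item sits awkwardly with that advice.
- **A reader might infer a bias towards declaring non-inferiority.** The documents do not support a direction, since the protocol gives grounds for either arm completing more.
- **The primary time point is contested.** If the Abstract's week 4 prevails, the primary result should be untouched and the point concerns only later follow-up. It does not vanish, because the week-16 comparisons are planned in any event.
- **Retention is not neglected.** WeChat contact may run to week 16, the general line on incentives leaves room for more, the sample size allows for 20% dropout, and multiple imputation with sensitivity analyses is planned. What stands is narrower: the one gift that is named comes before the assessment it should encourage.

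**Conclusion.** The point holds as a minor one. The trial plans to supply a back-related item after the 4-week treatment and before the week-16 pain score, and it names no gift tied to returning the week-16 questionnaire.

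A between-arm bias at week 16 needs three things together: the pad affects reported pain, receipt or use is not universal, and receipt or use differs between arms. None of these can be established from the documents. The bias is probably small against a margin of 1 NRS point, is zero if receipt and use are equal, and could go either way. The week-4 outcome should be unaffected, so the weight of the point also depends on how the conflict between week 4 and week 16 as primary time point is resolved. The change is worth making because it removes an avoidable ambiguity at almost no cost, not because the trial's conclusion is shown to be at risk.

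**What to change.** Reword the gift sentence in {18b} in one of two ways:

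1. replace the pad with a gift of the same value that has nothing to do with back pain; or
2. keep the pad but hand it over only after the week-16 questionnaire has been returned.

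In either case, give it to every randomised participant who returns that questionnaire, whether or not training was completed. For example: *Each randomised participant who returns the week-16 questionnaire will receive a gift worth about 50 yuan, irrespective of the number of training sessions completed.*

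**Cost.** The unit value is unchanged at about 50 yuan; total spending may change slightly, because the people who qualify are defined differently. The work is one protocol sentence and the matching participant information. The drawback is that nothing is given at week 4. If a week-4 reward is wanted, the value can be split between the two assessments, with any week-4 part unrelated to back pain. The Trial status section describes recruitment as still planned, so the change is simplest if made before it starts.
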